## Abstract

**Background:**

Recent years have seen a growing interest in the use of digital tools for delivering person-centred mental health care. Experience Sampling Methodology (ESM), a structured diary technique for capturing moment-to-moment variation in experience and behaviour in service users’ daily life, reflects a particularly promising avenue for implementing a person-centred approach. While there is evidence on the effectiveness of ESM-based monitoring, uptake in routine mental health care remains limited. The overarching aim of this hybrid effectiveness-implementation study is to investigate, in detail, reach, effectiveness, adoption, implementation, and maintenance as well as contextual factors, processes, and costs of implementing ESM-based monitoring, reporting, and feedback into routine mental health care in four European countries (i.e., Belgium, Germany, Scotland, Slovakia).

**Methods:**

In this hybrid effectiveness-implementation study, a parallel-group, assessor-blind, multi-centre cluster randomized controlled trial (cRCT) will be conducted, combined with a process and economic evaluation. In the cRCT, 24 clinical units (as the cluster and unit of randomization) at eight sites in four European countries will be randomly allocated using an unbalanced 2:1 ratio to one of two conditions: (a) the experimental condition, in which participants receive a Digital Mobile Mental Health intervention (DMMH) and other implementation strategies in addition to treatment as usual (TAU) or (b) the control condition, in which service users are provided with TAU. Outcome data in service users and clinicians will be collected at four time points: at baseline (t_0_), 2-month post-baseline (t_1_), 6-month post-baseline (t_2_), and 12-month post-baseline (t_3_). The primary outcome will be patient-reported service engagement assessed with the service attachment questionnaire at 2-month post-baseline. The process and economic evaluation will provide in-depth insights into in-vivo context-mechanism-outcome configurations and economic costs of the DMMH and other implementation strategies in routine care, respectively.

**Discussion:**

If this trial provides evidence on reach, effectiveness, adoption, implementation and maintenance of implementing ESM-based monitoring, reporting, and feedback, it will form the basis for establishing its public health impact and has significant potential to bridge the research-to-practice gap and contribute to swifter ecological translation of digital innovations to real-world delivery in routine mental health care.

**Trial registration:**

ISRCTN15109760 (ISRCTN registry, date: 03/08/2022).

**Supplementary Information:**

The online version contains supplementary material available at 10.1186/s12888-024-05839-4.

## Contributions to the literature

The present hybrid effectiveness-implementation study will improve our understanding of strategies, contextual factors, processes, outcomes, and costs of implementing ESM-based monitoring, reporting and feedback into routine mental health care.The DMMH reflects a step change in regulatory-compliant delivery of ESM-based monitoring, reporting and feedback as a technology-enabled service, facilitated by technological, user- and stakeholder-centred implementation strategies.The study will advance true person-centred care, empowering service users as active partners in treatment, self-management, and decision-making.Coupled with the work carried out in the wider EU IMMERSE consortium, the study will contribute to the digital transformation of mental health care in Europe.

## Background

Recent years have seen a growing interest in the use of digital tools for delivering person-centred mental health care [1, 2]. Experience Sampling Methodology (ESM) is a structured diary technique for collecting intensive longitudinal data on moment-to-moment variation in experience and behaviour in service users’ daily life and, as such, identifies them as experts of their own experience [1–3]. ESM therefore reflects a particularly promising avenue for adopting a person-centred approach through digital monitoring, reporting, and feedback in routine mental health care [1, 2, 4]. Such an ESM-based, person-centred approach may strengthen service user engagement and empowerment by making service users active partners in, rather than passive recipients of their own treatment and care [1, 2, 4]. It may further improve self-management and recovery, as it provides service users with a tool to enhance their understanding of, and better manage their own mental health problems [5, 6]. The ESM-based, person-centred approach may also provide goal direction in clinical assessment and management of care, as the detailed information on patterns of variation in, co-variation of symptoms, key problem areas and relevant contexts will help clinicians and service users to set clear, actionable and personalized therapy goals [4]. Finally, this approach may enhance shared decision making, as it provides strongly needed and relevant day-to-day information on key problem areas and relevant contextual factors as a basis for jointly making treatment decisions and evaluating progress of treatment [4].

While there is evidence on the effectiveness of ESM-based monitoring, reporting, and feedback in people with mental health problems [5, 7–9], uptake remains limited due to a lack of digital tools that comply with regulatory requirements and, hence, would allow for ESM-based monitoring, reporting, and feedback in routine care settings [2, 10–12]. Several regulatory, technological, clinical and organizational implementation barriers need to be addressed and overcome to realize more fully its potential through developing and evaluating strategies for effective implementation in mental health care practice [10, 12, 13]. In fact, research on the implementation of mHealth tools in routine mental health care in general remains very limited [12], which may explain the marked research-to-practice gap [10, 11]. The current hybrid effectiveness-implementation study [14] sets out to directly address this challenge as part of the EU Horizon 2020 funded Implementing Mobile MEntal health Recording Strategy for Europe (IMMERSE) consortium.

The overarching aim of this hybrid effectiveness-implementation study is to investigate, in detail, strategies, contextual factors, processes, outcomes, and costs of implementing ESM-based monitoring, reporting, and feedback into routine mental health care through a Digital Mobile Mental Health intervention (DMMH) and other implementation strategies to facilitate its use in four European countries (i.e., Belgium, Germany, Scotland, Slovak Republic). To this end, a pragmatic parallel-group cluster randomized controlled trial (cRCT) will be conducted and combined with a process and economic evaluation. The DMMH as the core strategy for implementing ESM-based monitoring, reporting, and feedback consists of (1) the MoMent App [2, 15], a digital application for mobile devices using ESM to systematically monitor service users’ self-reported momentary key complaints, symptoms, mood, activities, context, and treatment goals in daily life; and (2) the MoMent Management Console that allows clinicians to (a) personalize treatment goals and questionnaires that are presented by the MoMent App jointly with the individual service user, and (b) generate reports that provide meaningful information from the self-report data using the integrated MoMent Dashboard, an interface to visualize and distil the collected data into tailored feedback to the service users and their clinicians. Implementation strategies will further include technological strategies, strategies for clinicians and service users, and organisational strategies to facilitate the use of ESM-based monitoring, reporting and feedback in routine care via the DMMH. These will be standardized with some variation and flexibility in their application across sites.

To achieve our overarching aim, this study will:Establish, in a pragmatic cRCT of the DMMH and other implementation strategies to support its use in service users and clinicians in routine care settings, i) **R**each (i.e., service user participation), ii) **E**ffectiveness (defined as the interaction of efficacy and implementation in real-world settings), operationalized as greater service user engagement at 2-month post-baseline in the experimental than control condition as primary outcome, iii) **A**doption (i.e., proportion of service users and clinicians having used DMMH components in routine care), iv) **I**mplementation (defined as delivery of the DMMH as intended in routine care) and v) **M**aintenance (defined as the extent to which the DMMH becomes sustainable part of routine care at 6-month and 12-month post-baseline). Consistent with the **RE-AIM** framework [16], this will provide the basis for assessing the public health impact of implementation and scale-up of ESM-based monitoring, reporting and feedback via the DMMH and other implementation strategies. The primary hypothesis will be that, compared with the control condition (i.e., Treatment-As-Usual (TAU)), patient-reported service engagement, assessed with the total score of the Service Attachment Questionnaire (SAQ) at 2-month post-baseline (primary outcome), will be higher in the experimental condition (DMMH + additional implementation strategies + TAU), while controlling for service user engagement and clinical unit at baseline (please see our preregistration published on the Open Science Framework (OSF) [15] for further details on all hypotheses).Understand how service users leverage DMMH to support their health and well-being, and evaluate the process of implementing ESM-based monitoring, reporting and feedback in routine clinical care pathways using a realist evaluation framework [17] to identify in vivo configurations of contexts, processes and mechanisms of action, and how these are associated with outcomes of implementation in service users, clinicians, and managers/system administrators.Investigate the economic costs of the DMMH and other implementation strategies, and determine their cost-effectiveness and cost-utility vis à vis TAU.

## Methods

### Study design

In this hybrid effectiveness-implementation study [14], a parallel-group, assessor-blind, multi-centre cRCT will be conducted, in which 24 clinical units (as the unit of randomization) at eight sites in four European countries are randomly allocated using an unbalanced 2:1 ratio to one of two conditions: (a) the experimental condition, in which participants receive the DMMH and other implementation strategies in addition to treatment as usual (TAU) or (b) the control condition, in which participants are provided with TAU. Outcome data in service users and clinicians will be collected by assessors masked to random allocation of clinical units at four time points: at baseline (t_0_), 2-month (t_1_), 6-month (t_2_) and 12-month post-baseline (t_3_). The cRCT will follow Consolidated Standards of Reporting Trials (CONSORT) reporting guidelines [18] and relevant extensions [19, 20]. Standard Protocol Items: Recommendations for Interventional Trials (SPIRIT) [21] and Template for Intervention Description and Replication (TIDiER) [22] checklists are available as Supplementary Materials 7 and 8. The primary outcome will be patient-reported service engagement assessed with the SAQ at 2-month post-baseline, a measure of service users’ experience of, and engagement with, their treatment and service [23]. The cRCT will be combined with a process and economic evaluation to provide in-depth insights into in-vivo context-mechanism-outcome configurations as well as economic costs of implementing the DMMH in routine care.

### Study population and clusters

Service users and clinicians comprise the study population in the cRCT, process and economic evaluation in the four European countries, which will be recruited from three clinical units (clusters) in each of the eight clinical sites and, thus, a total of 24 units (clusters). Due to differences in mental health care systems across the four European countries, clinical units (clusters) will vary in structure, service type, and size, which will enhance generalizability of findings and allow implementation to be examined under various conditions. Clinical units (as cluster and unit of randomization) will be community mental health teams (Scotland), tracks (Germany (at the Central Institute of Mental Health Mannheim (CIMH)), inpatient, outpatient and community-based services (Germany (at Psychiatric Centre Nordbaden), Belgium, and Slovak Republic). A clinical unit typically will comprise a multidisciplinary team (i.e., psychiatrists, psychologists, nurses, social workers, occupational therapists). In each of the eight clinical sites, 54 service users will be recruited from three clinical units (i.e., 18 service users per unit), and thus a total of 432 service users (*n*=288 in the experimental condition, *n* =144 in the control condition). In addition, around 100 clinicians of these service users from 24 clusters across all sites are estimated to be recruited in a period of 6 months (see Fig. 1). Recruitment and consent procedures as well as eligibility criteria are described in more detail in Supplementary Material 2.

**Fig. 1 Fig1:**
[figure not shown]
Flow chart

### Experimental and control condition

#### Control condition: treatment as usual (TAU)

Participants in the control condition will be provided with TAU (i.e., continue to receive all the treatment they received prior to the start of the study). This will include good standard care delivered according to local and national service guidelines and protocols by their general practitioner, psychiatrist and other mental health professionals. Service contacts will be assessed for the duration of the trial using the Client Service Receipt Inventory (CSRI) [24] to monitor variation in delivery of, and engagement with, mental health services and digital technology.

#### Experimental condition: DMMH + additional implementation strategies + TAU

The DMMH and additional implementation strategies supporting its use will be provided in clinical units allocated to the experimental condition in addition to TAU. The DMMH reflects the core strategy for implementing ESM-based monitoring, reporting, and feedback in routine care and consists of (1) the MoMent App and (2) the MoMent Management Console (see above), which are hosted on the Therapy Designer platform by the movisens GmbH (Karlsruhe, Germany). In addition, technological implementation strategies, implementation strategies for clinicians and service users, and organisational implementation strategies will be delivered to facilitate the use of ESM-based monitoring, reporting and feedback in routine care via the DMMH. Both DMMH and additional implementation strategies are described in detail in Supplementary Materials 3 and 7.

The DMMH and additional implementation strategies will be delivered over a 6-month period, including an initial 2-month period for focused delivery of DMMH and implementation strategies, in which service users will be asked to use ESM-based monitoring via the MoMent App, and both service users and clinicians will be provided with detailed numeric and visual reporting and feedback via the MoMent Dashboard (in addition to basic visual feedback via the MoMent App) for at least four weeks. In the remainder of this 6-month period, service users and clinicians will continue to have access to the DMMH and additional implementation strategies. After the end of this period, there will be a 6-month maintenance period, in which service users and clinicians still have access to the DMMH but additional implementation strategies for service users and clinicians requiring active support by the research team will be discontinued.

### Outcome measures

Following the **RE-AIM** framework [16], the evaluation in this hybrid effectiveness-implementation trial will focus on a range of outcomes relating to **R**each, **E**ffectiveness, **A**doption, **I**mplementation, and **M**aintenance of the DMMH, covering service user experience, implementation outcomes, and mental health outcomes. The primary outcome has been selected for investigating the **E**ffectiveness of implementing the DMMH. The primary outcome will be patient-reported service engagement assessed with the SAQ total score [23] at 2-month post-baseline, a measure of service users’ experience of, and engagement with, their treatment and service. It captures a proximal effect of DMMH implementation on service users’ interaction with mental health services and, hence, reflects a primary indicator of implementation success. All primary and secondary outcomes will be assessed at baseline (t_0_), 2-month (t_1_), 6-month (t_2_) and 12-month post-baseline (t_3_). Secondary outcome data collected using ESM will follow the protocol from previous experience sampling studies [1]. Please see Supplementary Material 1 (based on SPIRIT statement) and Supplementary Material 4 for details of all measures used to examine reach, effectiveness, adoption, implementation, and maintenance. The assessment of safety based on the EU Medical Device Regulation (MDR 2017/745) is described in Supplementary Material 5.

### Process evaluation

A process evaluation will be performed using semi-structured interviews with service users, clinicians and managers/system administrators during or at the end of the initial 6-month period. The interviews of the process evaluation will be semi-structured and take a realist evaluation approach [17], which will be combined with the Non-adoption, Abandonment, Scale-up, Spread, and Sustainability (NASSS) framework [25] to establish what works, for whom, in what circumstances, in what respects, to what extent, and why. This implies that configurations of contextual factors, mechanisms of implementation, and outcomes of the implementation and intervention are explored across all levels of agents within the intervention and its implementation (i.e., individual participants, clinicians, managers and system administrators, and socio-economic and contextual factors that may impact their intentionality, behaviour and decision making at different stages of the intervention). This will also allow us to examine how service users and clinicians appropriate DMMH to serve their particular needs. Initial programme theories will be developed based on initial semi-structured interviews. Overarching programme theory and accompanying context-mechanism-outcome configurations will be tested among intervention users (individual interviews with participants who have completed the DMMH) as well as those who deliver the intervention (i.e., clinicians) and providing the context of intervention delivery (i.e., managers/system administrators), through iterative data collection. We will also explore unexpected consequences (positive or negative) on service users and health care professionals, such as impacts on clinical teams and organizations. Taken together, this will allow us to identify key aspects of successful and effective implementation of the DMMH in routine clinical pathways and treatment settings.

### Randomization and blinding

A validated and concealed procedure for randomization will be applied independently of the research team using an unbalanced 2:1 ratio for allocating clinical units to the experimental and control condition stratified by the eight clinical sites without contamination (cross-exposure to the experimental condition). An unbalanced allocation ratio of 2:1 will be used to allow for more detailed investigation of implementation aspects and protect against attrition. This will include an option in the concealed randomization procedure to allocate additional clinical units at each of the eight clinical sites if recruitment rates are lower than expected for some clinical units.

After random allocation of clinical units, clinicians in the experimental condition will be informed about allocation status. This will be done through an independent researcher and not the outcome assessors, who will be blind to allocation status for assessments at baseline, 2-month, 6-month and 12-month post-baseline. Further, there will be an independent contact person, who will not be involved in any assessments, for any questions regarding the recruitment and assessment procedure by service users and clinicians. The trial cannot be fully “blind” because clinicians and service users cannot be masked towards the allocation of clinical units to the experimental or control condition. However, outcome assessors will be blinded to allocation status when assessing eligibility, baseline scores and outcomes at baseline, 2-month, 6-month and 12-month post-baseline. Any data specific to the experimental condition (e.g., on clinical feasibility) will be stored in a separate database. Any breaks in masking will be documented in the trial master file and another blinded assessor will be allocated to repeat the assessment and complete the next set of assessments where possible. To maintain the overall quality and legitimacy of the trial, code breaks will only be done in exceptional circumstances when knowledge of the treatment allocation is absolutely essential for further management of the service user.

Given outcome data will be collected using ESM at baseline, 2-month, 6-month and 12-month post-baseline, and ESM forms a key part of the DMMH (as the experimental manipulation of the cRCT), we will control for any potential confounding of ESM *outcome* data collection by randomly allocating service users to either participation in collecting outcome data (on momentary quality of life, social functioning, and mental ill-health) using ESM or no participation in ESM outcome data collection. This secondary randomization will use a 1:1 ratio in a validated and concealed procedure that will be applied independently of the research team. Notably, this randomization does *not* address any of our study aims on reach, effectiveness, adoption, implementation, and maintenance but will control for (and investigate in sensitivity analyses) the potential effect of ESM data collection (by including a covariate on random allocation to participation in ESM outcome data collection in our statistical models for testing hypotheses on primary and secondary outcomes). The period of additional ESM data collection is independent of the use of the DMMH and other implementation strategies (as the experimental condition of the cRCT). Please see Supplementary Material 4 for further detail.

### Sample size calculation

We will test the primary hypothesis of the effect of the experimental vs. control condition (i.e., DMMH + additional implementation strategies + TAU vs. TAU) on service engagement as primary outcome (measured with the patient-reported SAQ total score as the dependent variable). We will use a fixed effects regression model controlling for unit effects, with a dummy variable for the condition (DMMH + additional implementation strategies + TAU vs. TAU), the SAQ engagement total score at baseline, and a dummy variable coding for the random allocation to ESM data collection at baseline. Ignoring in a first step the correlations between values taken from the same cluster, the total number of service users required to detect an effect of size d=0.4 (i.e., an effect size slightly lower than reported for service engagement in a previous study investigating the effects of an App-based mobile mental health solution [26]), with power 1- β = 0.80 at an alpha level of 0.05 with sample size ratio 2 (experimental condition) : 1 (control condition) is computed to be N0 = 201 for the null hypothesis that the difference between both experimental and control condition in terms of the mean SAQ score is zero at 2-month (t_1_) post-baseline, versus the alternative hypothesis that there is a difference (non-directional alternative). The statistical test will employ a fixed effects linear regression model with a variable representing treatment vs. control as the focal coefficient. The coefficient test will be performed at significance level α = 0.05, with the SAQ score at baseline as control variable and controlling for unit clustering. If all 24 units to be randomized have size n0 = (201/24=) 8.38 and assuming an intraclass coefficient of ICC = 0.05 [27], then N0 has to be increased to account for the effect of clustering by a factor of DEFF = 1+7.38×ICC = 1.37 for unit clustering. After appropriate upward rounding, this yields a total sample size of *N* = 288 service users, of whom 16 × 12 = 192 will be randomly assigned to the experimental condition (DMMH + additional implementation strategies + TAU) and 8 × 12 = 96 to the control condition (TAU). Further, based on previous research by IMMERSE partners and a meta-analysis investigating attrition in smartphone-based interventions [28], we expect an attrition of 35.5% from inclusion to 2-month post-baseline. For each of the eight clinical sites, this implies that a minimum of 54 service users will be recruited from three clusters (i.e., *n*=18 service users per cluster) and thus a total sample of 432 service users across all sites at baseline (i.e., with *n*= 16 × 18 = 288 in the experimental condition, *n* = 8 × 18 = 144 in the control condition), which allows for a 35.5% attrition rate to detect a medium effect size of d = 0.4 (with a power of 0.80, ICC=0.05, and α = 0.05). We will allow for an increase in recruitment target at all sites to up to *n*=108 per site (i.e., 36 service users per cluster) in order to compensate for delays in recruitment that may lead to overall under-recruitment across sites.

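### N0 = 201 does not follow from the stated 2:1 allocation: it matches 1:1, while 2:1 needs 223 to 225, so the stated 80% power is not met on the stated inputs

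*Protocol article*

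**What the plan says.** All the inputs are in the protocol article, Sample size calculation. The target is "the total number of service users required to detect an effect of size d=0.4", "with power 1- β = 0.80 at an alpha level of 0.05", tested "versus the alternative hypothesis that there is a difference (non-directional alternative". The first step sets clustering aside ("Ignoring in a first step the correlations between values taken from the same cluster"), and the result, "with sample size ratio 2 (experimental condition) : 1 (control condition) is computed to be N0 = 201", is tied explicitly to the 2:1 ratio.

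That number then drives the rest of the section. It is spread over the units ("If all 24 units to be randomized have size n0 = (201/24=) 8.38"), combined with the clustering assumption ("assuming an intraclass coefficient of ICC = 0.05") and inflated ("DEFF = 1+7.38×ICC = 1.37 for unit clustering"). The product is rounded up to 288 analysed (192 and 96). With 35.5% attrition expected, the recruitment target becomes 432 (288 and 144). The section closes by claiming power 0.80 for d = 0.4 with this design.

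The Randomization and blinding section shows that 2:1 is deliberate: it was chosen to study implementation in more detail and to protect against attrition.

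**The concern.** For a fixed total, unequal allocation gives a less precise treatment contrast than equal allocation. At 2:1 the variance of the difference in means is 9/8 of its value at 1:1, so about 12.5% more participants are needed for the same power. For d = 0.4, α = 0.05 and 80% power, a familiar total is 200 at 1:1. A total of 201 at 2:1 is almost the same number and leaves no room for the 9/8 factor.

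The cluster size, the design effect, the 288, the 432 and the headline power for the primary hypothesis all rest on N0. If N0 is too small for the stated ratio, the power claim is too high before any other assumption is examined.

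**Working it through.** **Inputs** (protocol article, Sample size calculation): d = 0.4 with SD = 1; two-sided α = 0.05; power 0.80; allocation k = 2; N0 = 201, i.e. 134:67; 24 units; ICC = 0.05; DEFF = 1.37; 288 analysed, i.e. 192:96.

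**1. Trying to reproduce 201.** For a comparison of two means with allocation k:1, the normal approximation to the total is

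N = [(1 + k)² / k] × (z₀.₉₇₅ + z₀.₈₀)² / d², with (1.960 + 0.842)² = 7.849 and 7.849 / 0.16 = 49.06.

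- k = 1: 4 × 49.06 = 196.2
- k = 2: 4.5 × 49.06 = 220.7

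Rounded up to whole groups, and with the exact noncentral t alongside:

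| Variant | Normal approximation | Noncentral t |
|---|---|---|
| 1:1, two-sided | 198 | 199 minimum; 200 as 100 + 100 (power 0.804) |
| 2:1, two-sided | 222 (148:74) | 223 minimum; 225 as 150:75 (power 0.804) |
| 1:1, one-sided | 156 | 156 |
| 2:1, one-sided | 174 | 177 |

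Only the two-sided 1:1 row comes close to 201, which is the next multiple of three after 199 to 200. Spending up to 25 further degrees of freedom on covariates or units leaves the 199 and 223 unchanged, so the regression model's extra terms do not explain the gap through degrees of freedom.

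**2. Power of N0 = 201 at the stated ratio.** Noncentrality = 0.4 × √(134 × 67 / 201) = 0.4 × √44.67 = 2.673. Normal approximation: Φ(2.673 − 1.960) = 0.762. Noncentral t: 0.758. At 80% power, 134:67 detects d of about 0.42.

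**3. Does rounding up to 288 repair it?** The plan's route is 201 × 1.37 = 275.4; 275.4 / 24 = 11.5, rounded up to 12 per unit; 24 × 12 = 288. Taking the plan's own design effect (1.369 before rounding), the effective size is 288 / 1.369 = 210.4. Noncentrality = 0.4 × √(210.4 × 2/9) = 2.735. Power is 0.781 (normal) or 0.777 (t). The detectable effect at 80% power is 2.802 × √(4.5 / 210.4) = 0.41. At 1:1 the same 210.4 would have power 0.823, so rounding does cover the target at 1:1 but not at 2:1.

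**4. The plan's own steps from a correct N0.**

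- 225 / 24 = 9.375 per unit
- DEFF = 1 + 8.375 × 0.05 = 1.419
- 225 × 1.419 = 319
- 319 / 24 = 13.3, rounded up to 14 per unit; 24 × 14 = 336 analysed

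Starting from 222 instead gives 222 × 1.4125 = 314 and again 336.

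**5. Effect of baseline adjustment, if it were credited.** Multiplying the required total by (1 − r²), where r is the correlation between baseline and 2-month SAQ, and rounding to whole 2:1 groups (normal approximation): r = 0.2 gives 213, r = 0.3 gives 201, r = 0.4 gives 186, r = 0.5 gives 168. No value of r is stated, so this is a range and not a result.

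**The case against.** The strongest reply is that the primary model is not an unadjusted t-test. Both the Sample size calculation and Statistical analysis sections include baseline SAQ as a covariate. If d is standardised by the unadjusted SD, a correlation of about 0.30 gives N0 = 201 at 2:1, and about 0.24 restores 80% at 288 under the plan's design effect (1 − r² = 210.4 / 223 = 0.943). Real power may therefore reach or exceed 80%. That stands as a statement about the trial. It does not rescue the calculation, because the section gives no correlation and claims no variance reduction in N0.

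Second, the 1:1 origin of 201 is an inference from the numerical match. This is fair. The error does not depend on it: whatever the origin, 201 is not what the stated inputs yield.

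Third, 75.8% is the power of an intermediate number, since the trial never analyses 201 people, and 288 at 2:1 with no clustering at all would have 89%. This is also fair. The figure that matters for the design is the 78% at 288, a loss of about 2 points, with part of the error absorbed by rounding up.

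Fourth, recruitment may rise to 108 per site. The article offers that to compensate for recruitment delays and under-recruitment, not to correct power, and 54 per site remains the stated minimum.

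**Conclusion.** The concern holds. On the inputs the article states, N0 at 2:1 is 223 to 225 (222 by the normal approximation), not 201. The stated 0.80 becomes 75.8% at 134:67 and about 78% at 192:96 with the plan's design effect of 1.37. Carried through the plan's own steps, the analysed total would be 336 rather than 288.

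These figures assume an unadjusted comparison with SD = 1 and take the plan's ICC, design effect and 288 completers as given. They do not use two further questions that deserve separate attention: the design effect is computed at 8.38 per unit although 12 per unit are to be analysed, and 432 × (1 − 0.355) = 279 falls short of 288.

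The isolated loss is modest, but it sits in the headline power claim for the primary hypothesis and should be corrected.

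**What to change.** - Replace N0 = 201 with the figure for 2:1: 223, or 225 in whole 2:1 groups (150:75). Recompute the cluster size, design effect and totals that follow from it.
- Restate the power, or the detectable effect, for the sample actually planned (432 recruited, 288 analysed). Under the plan's own design effect and without covariate credit, that is about 78% power for d = 0.4, or 80% power for d of about 0.41.
- If a gain from baseline SAQ is intended, state the assumed correlation between baseline and 2-month scores and its source, say which SD standardises d, and base the restated power on it, preferably with a range.
- Make the same correction in the statistical analysis plan wherever it repeats these figures.

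The cost is a change of text and a slightly less favourable power statement. The 2:1 ratio, the recruitment target and the analysis can all stay. Going to 336 analysed would be needed only if the sponsor wishes to keep 80% by the plan's own method without covariate credit.
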